### Sample Size

The sample size in this study was calculated based on the formula for unpaired categorical-numerical comparative research involving a single numerical measurement between 2 groups [27]. The parameters used included a significance level (α) of .05 and a power (1−β) of 90%, corresponding to Zα=1.64 and Zβ=1.28, respectively. According to previous studies, the mean (SD) wound closure in the control group (standard dressing) was 0.266 (SD 1.183) cm. Meanwhile, the expected mean wound closure in the intervention group (honey dressing), based on prior research using honey in wound management, is 1.433 cm. Using these values, the estimated minimum sample size required was approximately 18 participants per group. The full calculation procedure is provided in Multimedia Appendix 1 [21].

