## Introduction

### Background

The condition known as deep neck space infection (DNSI) emerges when an infection spreads into the deep neck spaces. If left undiagnosed and improperly treated, this condition may become life-threatening [1]. In Spain, there were 9-15 DNSI cases for every 100,000 people in 2012 [2]. DNSI has a 10% to 20% incidence rate and can lead to life-threatening complications if there is excessive accumulation of fluid in the deep neck space. It can also worsen into a deep neck abscess [3]. In Taiwan, there were 196 cases of DNSI between 1996 and 2002, with 33 cases per year, with a mortality rate of 7.6% [4]. DNSI cases increased from 1 case in 2006 to 15 cases in 2015 in Scotland [5]. Meanwhile, from 2004 to 2015, deep neck abscesses had a mortality rate of 1.4% and a complication rate of 22% in Finland [6]. The prevalence is higher in low- and middle-income countries, such as in Mexico, where DNSI has a prevalence of 42 cases over 5 years, with an average of 8.4 cases per year and a mortality rate of 8% [7], and in Ghana, where the prevalence is 135 cases over 7 years (2013-2020) with a mortality rate of 12.6% [8].

Between January 2017 and June 2020, the Otorhinolaryngology-Head and Neck Surgery (ORL-HNS) Department of [name] in Indonesia had the highest number of DNSI cases (24) and the lowest number (8) per semester. With an average rate of mortality of 15% between 2018 and 2020, this number has been rising annually. For instance, in 2021, there were up to 41 patients with DNSI; in 2022, the total spiked to 63 patients; and in November 2023, there were 50 patients [9]. This mortality rate is comparatively greater than that of Bandung and other countries [9]. The average mortality rate was 12.4% from 2015 to 2019 [9]. According to all of the prior studies, men are more frequently affected than women, and while the age range varies from early childhood to adults, the majority of patients are adults.

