### Statistical Analyses

The Shapiro-Wilk test will be used to assess the normality of continuous data because the sample size is less than 50. For comparison of wound healing outcomes between the honey dressing and standard dressing groups at each time point (days 1, 7, and 14), either an independent *t* test or Mann-Whitney U test will be used, depending on data distribution. To analyze the overall effect of treatment over time and assess the interaction between treatment group and time, a generalized estimating equation analysis will be performed. A *P* value of <.05 will be considered statistically significant. All data will be analyzed using SPSS software version 25.0 (IBM Corporation) and presented in tables summarizing the changes on days 1, 7, and 14 (Figure 2).

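### The 18 per group rests on a one-sided 5% value that is declared nowhere; read as two-sided tests at P<.05, it gives about 82% to 84% power, not 90%

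*Protocol article*

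**What the plan says.** The Sample Size section uses a formula for comparing one numerical measurement between two independent groups. Its inputs are:

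- "a significance level (α) of .05 and a power (1−β) of 90" percent, "corresponding to Zα=1.64 and Zβ=1.28, respectively";
- for the control arm, "the mean (SD) wound closure in the control group (standard dressing) was 0.266 (SD 1.183) cm";
- for the honey arm, an expected mean that, "based on prior research using honey in wound management, is 1.433 cm".

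From these it concludes that "the estimated minimum sample size required was approximately 18 participants per group". The details are referred to Multimedia Appendix 1, which is not reproduced in the article text.

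The Statistical Analyses section compares the groups on days 1, 7 and 14 with an independent t test, or a "Mann-Whitney U test will be used, depending on data distribution". It adds generalized estimating equations for the treatment effect over time and the group-by-time interaction. The only decision rule is that a P "value of <.05 will be considered statistically significant". Neither section, nor any other part of the article, says whether the tests are one-sided or two-sided.

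**The concern.** A sample size calculation and the test it supports must use the same critical value. Here the calculation uses the one-sided 5% point, while the analysis rule gives a bare threshold of P<.05. Without a declaration to the contrary, that threshold is normally taken to apply to two-sided P values.

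Two things are at stake. First, the 90% figure would describe a test that is not going to be done. A reader facing a non-significant result would then take it as stronger evidence against a benefit of the assumed size than the design can supply. Second, the Results section says that data analysis is under way. While sidedness is unstated, the choice between one-sided and two-sided P values remains open after the results are visible.

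**Working it through.** **Inputs (all from the Sample Size section)**

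- Difference: 1.433 − 0.266 = 1.167 cm
- SD: 1.183 cm, taken as common to both arms
- Standardised difference: 1.167 / 1.183 = 0.986
- Zβ = 1.28 (90% power)
- Equal allocation, 18 per group

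**Step 1. Reproduce the plan's figure.** The formula is n per group = 2 × [(Zα + Zβ) × SD / difference]².

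With Zα = 1.64: 2 × [(1.64 + 1.28) × 1.183 / 1.167]² = 17.52, rounded up to 18. This matches the plan, so 1.64 is not a misprint; it is the value that produced the sample size.

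**Step 2. Same formula with the two-sided value.**

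With Zα = 1.96: 2 × [(1.96 + 1.28) × 1.183 / 1.167]² = 21.57, rounded up to 22. This does not give 18.

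**Step 3. Power at 18 per group.** The noncentrality is 0.986 × √(18/2) = 2.96, with 34 degrees of freedom for the t test.

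| Method | One-sided 5% | Two-sided 5% |
|---|---|---|
| Normal formula (as in the plan) | 90.6% | 84.1% |
| Noncentral t (the planned t test) | 89.5% | 82.0% |

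For the Mann-Whitney U test under normality, with an assumed relative efficiency of 3/π, two-sided power is about 80%.

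**Step 4. What 90% power would take with a two-sided test.**

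- Normal formula: 22 per group (44 in total).
- Noncentral t: 22 per group gives 89.2% and 23 gives 90.5%, so 23 per group (46 in total).

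**Step 5. Difference detectable with 90% power at 18 per group, two-sided.**

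- Noncentral t: standardised difference 1.112, and 1.112 × 1.183 = 1.32 cm.
- Normal formula: (1.96 + 1.28) × 1.183 × √(2/18) = 1.28 cm.

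Both exceed the planned 1.167 cm.

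**The case against.** **The article never says two-sided.** This is the strongest objection, and it stands as a limit on the claim. The anticipated finding is directional (the Discussion expects faster healing with honey). If a one-sided 5% test was intended, 18 per group gives about 90% power and the sum is correct for its inputs. The fault would then be an undeclared one-sided test. Either way, the Sample Size and Statistical Analyses sections need one common statement of sidedness.

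**Part of the gap is a change of method.** This is also fair. The plan uses the normal formula, and on that basis the two-sided power is 84.1%. The further fall to 82.0% comes from using the t distribution, under which even the one-sided design gives 89.5%. Within either method, sidedness alone costs between 6 and 8 points. Both two-sided figures exceed 80%.

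**Nothing in the design can change now.** All 36 participants are enrolled, and data collection is reported as complete. Two-sided testing at 5% leaves the type I error and the effect estimate untouched. That limits the remedy to the text, but the stated power will still be used to interpret the result.

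Two stronger readings are tempting, and the article does not support them:

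- *The group-by-time interaction proves that the tests are two-sided, because it has two degrees of freedom.* That requires time to be coded as a three-level factor, which the article does not say. The swab and biomarker outcomes are measured on days 1 and 14 only, so their interaction has one degree of freedom. Moreover, the sample size was set for a single two-group comparison, not for the interaction.
- *Power is really about 74%, because the Background reports "With an average rate of mortality of 15% between 2018 and 2020".* That figure is the department's mortality among patients with deep neck space infection. It is not a rate of non-evaluable participants in this trial. Power of 74% is what about 15 evaluable per group would give; it is an illustration under an assumed 15% loss and not a property of the plan. Preparing exactly 36 allocation slips is no error either.

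**Conclusion.** The point holds in conditional form. The 18 per group depends on a one-sided critical value that no part of the article declares. Under the natural two-sided reading of P<.05, power to detect 1.167 cm is about 82% to 84%, not 90%. The risk of missing a true effect of that size is therefore about 16% to 18% for the t test, against the stated 10%. With the Mann-Whitney U test it is about 20% under normality.

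These figures assume a common SD of 1.183 cm, normally distributed data and all 36 participants evaluable. The overstatement concerns planning power only; it does not invalidate the trial or bias its estimate.

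**What to change.** Keep the 36 patients and make three linked text changes.

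1. In Statistical Analyses, state that all tests are two-sided at the 5% level. Analysis is already under way, so date the statement.
2. In Sample Size, replace the power statement as a whole, including Zα, Zβ, the 90% and the claim that 18 is the resulting minimum. Suggested text: *With 18 per group and a two-sided 5% test, power is about 82% (84% by the normal approximation) to detect 1.167 cm (SD 1.183); the difference detectable with 90% power is about 1.32 cm.* Changing only 1.64 to 1.96 would create a new contradiction, because the formula with the remaining inputs yields 22.
3. Bring Multimedia Appendix 1 into line with the new statement.

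If attrition is mentioned, label any loss rate as an illustrative assumption.

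The cost is a text correction and a less favourable stated power. No patients, visits or measurements are affected.

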### Randomization

In the study we conducted, participants were assigned to the control and intervention groups using a comprehensive randomization technique. The distribution was carried out by concealing opaque envelopes with numbered slips ranging from 1 to 36. These slips were arranged in a box, and the sequence was chosen using the Microsoft Excel random generator. Importantly, the researchers remained blind to the randomization findings throughout the process.

The participants were then assigned to either the control group (standard dressing) or the intervention group (standard dressing plus Indonesian Nusantara honey). The resident doctor was responsible for administering the dressing and obtaining detailed randomization instructions.

### Blinding

This study was designed as a single-blind clinical trial. The principal investigator and the assistant who measured wound indicators remained blinded throughout the treatment period, and treatment allocation was disclosed only after the final database lock. Patients were not blinded, as full blinding was not feasible due to the intrinsic characteristics of honey. Its distinct color may stain the dressing material, and its recognizable odor may reveal the intervention. These factors could have led patients to infer their group allocation, making participant blinding impractical.

### Honey Sample

Honey has an extended record of enabling wound healing and offers a more affordable therapeutic option. This study used raw and unsterilized local honey known as Nusantara honey. Nusantara honey contains biological components and beneficial microorganisms that promote wound healing. As a result, the honey used in this study was not sterilized, as sterilization can diminish its benefits. The honey used in the study has already passed Indonesia’s food and drug administration test (known as BPOM) with the number MD 011167000300234. The same batch of honey is used in the study, ensuring the quality and safety of the product remain the same. It was confirmed to be safe because it passed the laboratory test at the Health Laboratory Calibration and Testing Center, Regional Health Office of Yogyakarta. The test results showed negative findings for fungal and bacterial cultures. The certificate, issued under number 009008/LHU/BLKK-Y/05/2024, confirmed that the honey sample met the safety standards for clinical application. Although sterilization was not performed to preserve its bioactive components, the honey was certified safe and free from harmful contaminants. This was validated by the extraction of samples following wound healing, where laboratory studies revealed the absence of toxins, fungus, or potentially hazardous bacteria.

In several previous studies, honey was used clinically, and the same brand has been applied in Indonesia. In studies in other countries, natural honey has been used without sterilization and has been shown to produce better results [23,28-35].

### Intervention Procedure

Both the control and intervention groups received wound care following the standard operating procedure established by the Laryngopharyngology Division, ORL-HNS Department, [name] Hospital. This protocol includes wound debridement, saline irrigation, application of gauze rolls, and administration of Prontosan. Necrotic tissue was removed, and the wound was disinfected using sodium chloride before a gauze roll soaked with antibiotic ointment was inserted to serve as drainage. Dressing frequency was determined based on the volume of pus produced—daily dressing was performed until pus production decreased to less than 5 cc, at which point dressings were changed every 3 days, eventually decreasing to once a week when no pus was observed.

In the intervention group, the standard protocol was followed with an additional intervention using Nusantara honey. A 120-cm gauze roll was immersed in 12 cc of Nusantara honey for approximately 1 minute, allowing full absorption before being applied to the wound and covered with sterile gauze. Prontosan gel was used when pus was no longer present to stimulate granulation tissue formation until the wound base reached the surface. Wounds were generally left to heal by secondary intention, unless primary closure or reconstruction was necessary due to extensive tissue loss.

Monitoring of adverse events was conducted directly by the principal investigator and otorhinolaryngology residents during each wound dressing session. If the honey dressing failed to achieve adequate wound healing outcomes, a swab was taken from the wound base for repeat sensitivity culture. The wound care protocol was then reverted to the standard dressing procedure used at [name] Hospital, followed by further management based on the patient’s condition, including the treatment of any comorbidities that might hinder the healing process. The antibiotic protocol applied to both the control and intervention groups included ceftriaxone and metronidazole upon initial presentation, with adjustments made according to the culture results when available. In cases of infection escalation, antibiotics were modified following the hospital’s infection control guidelines. The average wound healing time was 7 days, although some cases required up to a month or additional surgical interventions, such as grafting.

### Measurements

Table 1 outlines the schedule for data collection. All participants who were intervened on had data collected on days 1, 7, and 14. The data comprised measurements of bacterial colony counts, wound size, Bates-Jensen Wound Assessment Tools (BWATs), proinflammatory cytokines, and growth factors. The data are intended to reflect the effects of interventions performed on wound healing in each stage.

**Table 1 table1:** Schedule for data collection.

Activity		Timeline (days)
Filling out the case report form		1, 7, and 14
Wound measurement		1, 7, and 14
Measuring BWATs^a^ (size, depth, edges, undermining, necrotic type, necrotic amount, exudate type, exudate amount, skin color, edema, induration, granulation, and epithelialization)		1, 7, and 14
Taking a wound bed swab		1 and 14
Taking wound tissue (biopsy)		1 and 14
Vital sign examination (blood pressure, respiratory rate, heart rate, temperature, SPO2^b^, and VAS^c^)		1-14 (daily)
**Supporting examinations**		
	Complete blood count^d,e^	1-14 (daily)
	Computed tomography scan^e^	1 and 14
	Chest X-ray^e^	1 and 14
	Blood gas analysis^e,f^	1, 4, 7, 10, and 14
Monitoring complications		1-14 (daily)
Pus culture aspiration (bacterial, sensitive to antibiotic, intermediate to antibiotic, or resistant to antibiotic)		1 and 14
Wound bed culture (bacterial, sensitive to antibiotic, intermediate to antibiotic, or resistant to antibiotic)		1 and 14
Measurement of growth factors and cytokines (IL-1, TNFα, and VEGF)		1 and 14

^a^BWAT: Bates-Jensen Wound Assessment Tool.

^b^SPO2: saturated oxygen.

^c^VAS: visual analog scale.

^d^Complete blood count includes hemoglobin, red blood cells, white blood cells, and platelets. Other laboratory tests include blood ABO group and rhesus type, prothrombin time, activated partial thromboplastin time, international normalized ratio, total bilirubin, direct bilirubin, indirect bilirubin, serum glutamic oxaloacetic transaminase, serum glutamic pyruvic transaminase, albumin, sodium, potassium, chloride, blood urea nitrogen, urea, creatinine, uric acid, random blood glucose, fasting blood glucose, 2-hour postprandial glucose, hemoglobin A1C, and hepatitis B surface antigen.

^e^As long as the patient was still admitted in the ward.

^f^Arterial blood gas parameters include pH, partial pressure of carbon dioxide, bicarbonate, partial pressure of oxygen, and base excess.

Each parameter was measured following standardized procedures, and designated personnel were assigned to each task to minimize measurement bias and ensure internal validity.

On day 1, the following assessments were performed:

Wound size (length, width, and depth): Wound size was measured by a trained research assistant. The measurement was conducted with a specific ruler and probe. The width and length recorded were the largest calculated amounts, whereas the depth of the wound was measured using a specific probe inserted perpendicularly to the meeting point of the length and width until it reached the base of the wound. To enhance measurement precision and reproducibility, the ImitoMeasure wound documentation app was also used [36]. This mobile app enables photographic documentation with calibrated scale indicators, providing consistent digital measurements of wound area and depth. This measurement was conducted by the research assistant 3 times, and the results were averaged to obtain a more accurate wound size estimate.BWAT: The raw wound data and clinical wound appearance were first recorded by an assistant. The final scoring and interpretation based on these observations were conducted independently by the principal investigator, who was blinded to treatment allocation during the evaluation process.Wound swabs for bacterial culture: Infection was considered to have improved as evidenced by bacterial culture findings and the number of bacterial colonies that proliferated. Samples were collected by the clinical team under sterile conditions and submitted to a certified microbiology laboratory for quantitative colony count analysis. Samples were taken from the wound base using sterile cotton, placed in Amies transport medium, and delivered to a microbiological laboratory.Tissue biopsy for cytokine (IL-1 and TNF-α) and growth factor (VEGF) analysis: Tissue biopsy was performed by an otorhinolaryngology resident using standard sterile technique. The biopsy samples were then processed by trained laboratory personnel for immunohistochemical examination.

On day 7, wound size measurements and BWAT scoring were repeated using the same tools and by the same assessors as on day 1 to ensure consistency across time points.

On day 14, all baseline measurements were repeated, including wound size, BWAT scoring, wound swab cultures, and tissue biopsies for cytokine and growth factor quantification. The same assigned personnel performed all assessments to reduce interobserver variability and enhance the reliability of longitudinal comparisons. The schedule of interventions and sample measurements is illustrated in Figure 1.

**Figure 1 figure1:**
[figure not shown]
Study protocol items and schedule of assessments during the 14-day observation period.
The tests will be conducted as long as the patient is hospitalized.

### Outcomes

In this study, a research assistant collected samples after completing wound dressing and storing the dressing materials. Measurements were taken on the first, seventh, and fourteenth days for BWAT assessments, as well as the first and fourteenth days for bacterial colony identification from wound bed swabs and cytokine and growth factor expression analysis from tissue samples. The resident doctor was accountable for the dressing and performed pus aspiration and tissue sampling. All information was meticulously documented on an authorized form. Wound measures included length, width, and depth, with data based on the largest width and length. Wound depth was measured using a probe perpendicular to the wound’s length and width. BWATs were evaluated by an uninformed research assistant. Bacterial culture findings and the number of bacterial colonies were used as evidence of infection improvement. Swabs from the wound bed were delivered to the microbiology lab. Tissue samples were sent to the Anatomical Pathology lab for immunopathological examination of wound healing, including quantification of IL-1, TNF-α, and VEGF expression. Tissue samples were collected using nasopharyngeal biopsy forceps, and the preserved tissue was sent out for analysis. Additionally, laboratory examinations, radiographs, and patient comorbid factors were documented for analysis in the case report form.

### Statistical Analyses

The Shapiro-Wilk test will be used to assess the normality of continuous data because the sample size is less than 50. For comparison of wound healing outcomes between the honey dressing and standard dressing groups at each time point (days 1, 7, and 14), either an independent *t* test or Mann-Whitney U test will be used, depending on data distribution. To analyze the overall effect of treatment over time and assess the interaction between treatment group and time, a generalized estimating equation analysis will be performed. A *P* value of <.05 will be considered statistically significant. All data will be analyzed using SPSS software version 25.0 (IBM Corporation) and presented in tables summarizing the changes on days 1, 7, and 14 (Figure 2).

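### The day-1 baseline is tested as an outcome and enters the GEE only as a response; using it as a covariate would gain precision without more patients

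*Protocol article*

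**What the plan says.** The Statistical Analyses section of the protocol article gives three instructions.

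- Normality is checked by Shapiro-Wilk. There follows a "comparison of wound healing outcomes between the honey dressing and standard dressing groups at each time point (days 1, 7, and 14"). The t test for independent samples is one option; the article's words for the other are "or Mann-Whitney U test will be used, depending on data distribution".
- A GEE is then fitted, and its stated purpose is this: "To analyze the overall effect of treatment over time and assess the interaction between treatment group and time". No covariate is named. Read with the sentence before it, the responses are the values on days 1, 7 and 14.
- P below .05 counts as significant. Neither sidedness nor the deciding analysis is stated.

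The Measurements section calls the day-1 assessments baseline. Table 1 sets wound size and BWAT on days 1, 7 and 14, and cultures and tissue markers on days 1 and 14 only.

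The Sample Size section compares a single measurement between two groups, "corresponding to Zα=1.64 and Zβ=1.28, respectively". It states that "the mean (SD) wound closure in the control group (standard dressing) was 0.266 (SD 1.183) cm" and that "the expected mean wound closure in the intervention group (honey dressing), based on prior research using honey in wound management, is 1.433 cm". Wound closure is not defined there.

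**The concern.** In a randomised trial, a between-group test of a baseline value says nothing about treatment, because any difference is chance. The useful role of day 1 is as a covariate: it explains part of the patient-to-patient spread at follow-up and so narrows the interval for the treatment effect. The plan uses it in neither the per-visit tests nor, as written, the GEE.

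This matters more with 18 per arm and simple randomisation. The baseline difference between arms has a standard error of √(2/18) = 0.33 SD, so a chance imbalance above 0.5 SD arises in about 13% of such trials. An unadjusted day-14 comparison carries part of that imbalance as noise.

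Two further features deserve correction. A GEE group effect averaged over all three visits includes one at which no effect can exist. And choosing the test by Shapiro-Wilk leaves open whether the result is a difference in means or in ranks, which may vary by visit and outcome.

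**Working it through.** **Inputs.** From Sample Size: means 0.266 and 1.433 cm, SD 1.183 cm, Zα 1.64, Zβ 1.28, 18 per arm. Difference 1.433 − 0.266 = 1.167 cm; 1.167/1.183 = 0.986 SD. Not in the article, so assumed: the day 1 to day 14 correlation r, equal SD and correlation across visits, and roughly normal data.

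**Step 1: the plan's own figure.** n = 2[(1.64 + 1.28) × 1.183/1.167]² = 17.52, rounded up to 18. It reproduces, with 1.64 being the one-sided 5% point. One-sided power at 18 per arm is 90.6% (normal) or 89.5% (t).

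**Step 2: two-sided 5%, unadjusted.** SE = 1.183 × √(2/18) = 0.394; 1.167/0.394 = 2.959. Power = Φ(2.959 − 1.960) = 84.1%, or 82.0% by noncentral t. For 90% power, 22 per arm are needed (normal; 23 by t).

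**Step 3: what day 1 adds, taking 1.183 as the SD of the day-14 value.** Relative to the unadjusted comparison, the variance is 1 − r² with day 1 as covariate and 2(1 − r) for the GEE contrast of day 14 with day 1, which behaves like a change score. Power = Φ(2.959/√factor − 1.960).

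| r (assumed) | Adjusted: factor | Adjusted: power | Adjusted: n per arm for 90% | GEE contrast: factor | GEE contrast: power |
|---|---|---|---|---|---|
| 0.3 | 0.91 | 87% | 20 | 1.40 | 71% |
| 0.5 | 0.75 | 93% | 17 | 1.00 | 84% |
| 0.7 | 0.51 | 99% | 12 | 0.60 | 97% |

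By t with 33 degrees of freedom the adjusted figures are 85%, 91% and 98%. The ratio of the two factors is (1 − r²)/[2(1 − r)] = (1 + r)/2, which is below 1 for every r below 1. The contrast is therefore never better than adjustment, and below r = 0.5 it is worse than the plain day-14 comparison.

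**Step 4: a group effect averaged over three visits (illustration).** Assume effects of 0, 0.5 and 0.986 SD on days 1, 7 and 14. The average is 0.495 SD, against 0.743 SD over days 7 and 14 alone. The variance factor is (1 + 2r)/3, that is 0.667 at r = 0.5 and 0.80 at r = 0.7. Then 0.495/(0.333 × √factor) = 1.82 and 1.66, giving power of 44% and 38%.

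**Step 5: if 1.183 is instead the SD of change.** The day-14 SD is then 1.183/√[2(1 − r)].

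| r (assumed) | Day-14 SD (cm) | Raw day 14 | Change | Adjusted |
|---|---|---|---|---|
| 0.5 | 1.183 | 84% | 84% | 93% |
| 0.6 | 1.323 | 75% | 84% | 91% |
| 0.7 | 1.527 | 63% | 84% | 89% |

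**Step 6: the pre-test.** In simulation (8,000 runs, 18 per arm, two-sided), choosing the test by Shapiro-Wilk gave type I error of 5.1% for normal and 4.5% for lognormal data, and power of 81.5% against 81.7% for a plain t test.

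**The case against.** A reader might infer that the plan ignores day 1, biases its result, wastes power through the pre-test and is underpowered. The article does not support any of these.

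- **Day 1 is not ignored.** The GEE group-by-time interaction uses it, and above r = 0.5 its day-14 contrast beats the unadjusted test. What stands is that day 1 serves as a response, the less efficient use.
- **Validity is not at stake.** The standard error of an unadjusted test already allows for chance imbalance. The loss is in precision.
- **The pre-test costs almost no power** (Step 6). Its fault is only that the effect measure is not fixed.
- **A shortfall in power is conditional.** On the article's own one-sided input, 18 per arm meets 90%. The 82–84% applies only if P < .05 is two-sided, which is not stated.
- **Comparison of raw values, and sizing on change from baseline, are both inferences.** Closure is undefined, the results tables are said to summarise changes, and Figure 2 and the sample size appendix are not shown. One SD cannot serve both the change and the day-14 value unless r = 0.5, hence two sets of figures.
- **The correlation may be low.** The article gives average healing times of 14 days (Background) and 7 days (Intervention Procedure). If many wounds are closed by day 14, the correlation weakens and normal-theory power becomes rough. This caution stands in full.
- **Covariates are often left to an analysis plan.** That is fair for detail. The article itself, however, fixes the day-1 test and the choice of test by Shapiro-Wilk.

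**Conclusion.** The point holds as one of efficiency and clarity. Day 1 is tested where no treatment effect can exist, and it is not used where it would help.

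With a two-sided 5% test and 1.183 as the SD of the day-14 value, adjustment raises power from 84% by about 3, 9 and 14 points at r = 0.3, 0.5 and 0.7. It passes 90% from about r = 0.5. If 1.183 is the SD of change, the adjusted analysis keeps 93%, 91% and 89% at r = 0.5, 0.6 and 0.7, while the raw comparison falls to 84%, 75% and 63%. In both cases adjustment is at least as good as any alternative the plan names for the day-14 effect.

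The 38–44% for a three-visit average rests on an assumed day-7 effect and on one reading of the overall effect. It shows the direction of the dilution and is not a forecast of the trial's power.

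**What to change.** - **Wound size and BWAT:** analyse days 7 and 14 as responses in one model with treatment, visit, treatment-by-visit and the day-1 value as covariate. If GEE is kept, use a small-sample correction, since there are only 36 patients.
- **Outcomes measured on days 1 and 14 only** (colony counts, IL-1, TNF-α, VEGF): use ANCOVA on day 14 with the day-1 value as covariate.
- **Day-1 tests:** drop them and describe the baseline by arm.
- **Effect measure:** set it, and any transformation, in advance for each outcome in place of the Shapiro-Wilk choice. Keep Mann-Whitney as a sensitivity analysis. Say how closed wounds (size zero) are handled.
- **Reporting:** give the adjusted difference with its 95% CI, and state which analysis decides and whether the test is one- or two-sided.

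**Cost.** No new patients or measurements are needed. The Results section says analysis is under way, and the Blinding section discloses allocation only after database lock. The change therefore needs a dated amendment before disclosure; if allocation is already known, the adjusted analysis must be labelled post hoc. The gain will be small if the correlation proves low.
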